**Instruments: Outcome measures for adolescent**

## *Sedentary activity*

Weekly frequency and school day/weekend day duration of participation in common sedentary behaviours (TV viewing, playing electronic games, using a computer) and moderate/vigorous physical activity (sports, dance, active play) will be assessed using questions drawn from the Western Australian Child and Adolescent Physical Activity and Nutrition Survey and the Health Kids Queensland Survey [43-44].

## *Moderate/Vigorous Physical activity*

Time spent in moderate to vigorous intensity physical activity (PA) will be assessed over 7 days using a Actical accelerometer and pedometer worn on the hip. The MiniMitter Actical is the most widely used and validated accelerometer in studies of children and adolescents [45-46]. Seven days of accelerometer and pedometer measurement are recommended for the purposes of acceptable measurement of moderate to vigorous PA [46]. Total weekly PA as well as weekend PA and after school weekday PA will be assessed.

## *Food intake*

It is acknowledged that all methods of dietary data collection are fraught with limitations [47] and adolescents are known to be a particularly hard group from which to collect detailed and accurate dietary records [48-49]. Overweight adolescents tend to underreport their intake because of factors including lack of motivation, body image concerns, rebellion against authority and unstructured eating habits that make recording difficult [48, 50-51]. It is recommended that intervention studies for overweight participants use at least two types of dietary assessment tools [52] and for this study, adolescent nutrition will be assessed through collection of data from three day food records using weighed or household measures and an eating behaviour checklist that collects data on key eating behaviours. In national surveys 24 hour recalls are commonly used, however, in adolescents this measure tends not to reflect the wide variation in teen diets over several days [49]. Three day food records are the most appropriate tool in this instance to measure intake and allow for analysis of detailed nutrition information from a small sample group. The burden of recording for adolescents has been considered and food records have therefore been kept to three days to maximise participation. Food diary analysis will provide information about the number of serves of fruits, vegetables and extra foods, as described by the Australian Guide to Healthy Eating [53]. The total energy intake and intake of macronutrients and micronutrients will be determined using the AUSNUT database and Foodworks Professional edition version 3.02 software. Participants will also complete the eating behaviour checklist to provide information about their eating behaviours and perceived intake. This checklist will be used to give feedback to adolescents and based on questionnaires used in similar cohorts [54]. Questions include whether participants eat breakfast, how often they eat fast food and how often they eat meals with their family. All analysis will be completed by a qualified dietitian.

*Adiposity*

Weight, height and waist circumference measurements will be made using calibrated scales, stadiometer and inelastic tape measure and standardized protocols. Body mass index will be calculated and age and sex adjusted BMI z-scores determined to enable comparison with state-wide surveys (WA, QLD).

## *Fitness*

Cardiovascular fitness will be assessed using the modified incremental shuttle walk test [55] (University Hospitals of Leicester NHS trust, Leicester, UK). This test is based on the widely used incremental shuttle run test designed for healthy individuals [56], with the reduction of shuttle distance from 20m to 10m to provide a lower demand start to the test for those with health problems. Participants walk/run between markers in time with beeps. The beep interval decreases every minute, requiring increases in walking velocity. The test is terminated when the participant can no longer reach the end of the 10m in time with the beep. In obese adolescents test-rest reliability is very high (ICC=0.92) and validity has been demonstrated with strong correlations with other aerobic indices including maximal oxygen uptake in bicycle ergonometer tests (r=0.79) [57].

Strength of the quadriceps, biceps and deltoid muscles will be assessed using standard ‘break’ manual muscle testing protocols [58]. ‘Break’ tests require the participant to hold a position while the tester applies progressive resistance until the position is broken. Peak force will be recorded using a force transducer. All muscle testing will be performed on the non-dominant limb and each test will be performed 3 times, with an average score used for analysis. The testing positions for the myometer were modified from Backman et al. [59]. For quadriceps (knee extensors), participants will sit upright in a chair with thighs supported and hands rested lightly on the thighs, palms up. The participant will be directed to extend their non-dominant knee fully and the Myometer will be applied to the anterior lower limb just above the malleoli. The participant will try and maintain that position as the researcher applies resistance in the opposite direction. The dominant lower limb must remain still at all times [59]. For biceps (elbow flexors), participants will be positioned with their dominant arm relaxed by their side, with the non dominant hand in 90° of elbow flexion and supinated, The researcher will stabilise the non-dominant arm posteriorly superior to the elbow, ensuring the elbow remains free to move. The Myometer will be applied on the forearm just proximal to the radial styloid process. The participant will be instructed to keep their elbow flexed at 90° as resistance is provided by the researcher in the opposite direction.[59] For deltoids (shoulder abductors), participants will be seated with the non-dominant shoulder abducted to 90°, elbow extended, forearm in mid pronation with palm facing down. The dominant arm remains rested on the participant’s lap. The researcher will stabilise the non- dominant shoulder, ensuring the shoulder remains free to move. The Myometer will be applied to the upper limb approx 2cm proximal to the lateral humeral epicondyle. The participant will be instructed to maintain the testing position as resistance is provided by the researcher in the opposite direction [59]. Hand held force transducer tests of muscle strength have been shown to have good criterion validity in comparison to laboratory dynamometers, with good intra-tester and inter-tester reliability [60].

Muscle power will be assessed using a vertical jump protocol [61]. The participant will stand side on to the wall and reach as high as possible with their hand closest to the wall, feet flat on the ground; the height of the finger tips is measured. The participant then jumps vertically as high as possible using a knee bend and arm swing motion to assist in projecting the body. The participant attempts to touch the wall at the highest point of the jump. The distance between the standing reach height and the jump reach height is recorded. Three measures are taken and the highest recorded. Reliability has been reported to be high (ICC = 0.96) [62]. Vertical jump has been used to determine power outputs in obese adolescents [63].

## *Mental health*

The primary outcome measure will be depressive symptoms assessed using the Moods and Feelings questionnaire (MFQ) [64]. The MFQ is a 33 item self-report measure which looks at depressive symptoms in children and adolescents. It has good test-retest reliability [65] and has been validated with a clinical population [66].

*Motor coordination*

Motor competence will be assessed using Movement Assessment Battery for Children-2 (MABC-2 ) [67]. The MABC-2 comprises 8 tasks, three measuring manual dexterity, 3 measuring aiming and catching and 2 measuring balance. Age norms are used to determine a standard score based on a distribution with a mean of 10 and a standard deviation of 3. Separate standard scores can be determined for each of the sub-tests. Minimum value of the test-retest reliability of the original MABC is 0.75 and the inter-tester reliability is 0.70. The MABC has been found to correlate well with other movement tests [68-69].

## *Activity and food guideline behaviour, readiness to change and self efficacy*

Meeting of sedentary screen time, vigorous physical activity and key diet behaviours and readiness to change if not currently meeting recommended behaviours will be assessed using questions used in an adult obesity study [70] based on the transtheoretical model of health behaviour change [71]. This approach has been used successfully for childhood obesity [72] and the item have demonstrated good concurrent validity [70].

Self efficacy in relation to confidence in being able to exercise for 60 minutes every day and eat a healthy diet on a regular basis will be assessed using Bandura’s exercise self efficacy [73] and weight efficacy lifestyle [74] scales. The scales consist of 18 and 20 items respectively and cover different situational domains such as negative emotions, social pressure, physical discomfort and availability/external constraints. Participants rate their confidence in being able to maintain desired behaviour on a ten point scale from 0 (not certain) to 9 (very certain). The scales were slightly modified to reflect the target behaviours of the study as recommended [75]. The exercise self efficacy scale has demonstrated good psychometric properties, sensitivity to change over a 6 week intervention and correlation with objective functional status measures [73]. The weight efficacy lifestyle scale has demonstrated good internal consistency, sensitivity to change with a nine week intervention, and significant correlations with a related eating self efficacy scale [74].

*Attitudes to PA, Eating and Self*

Attitudes to PA will be assessed using the revised Physical Activity Enjoyment Scale (PAES) [76]. Internal consistency, test-retest reliability and construct validity has been demonstrated [77-79].

Attitudes to eating will be assessed with the Dutch Eating Behaviours Questionnaire (DEBQ) [80]. The DEBQ is a 33 item self-report measure of eating styles developed to increase understanding of eating patterns in obese individuals. The measure has three scales, restrained, external and emotional eating. This measure has been shown to have good internal consistency, discriminative and concurrent validity and factor stability [80-81]. This measure has also been demonstrated as appropriate for use in children over 12 years of age [82].

Harter’s Self-Perception Profile for Children (SPPC) [83] is a 36 item self-report measure of self-concept. The SPPC comprises five subscales; Scholastic Competence, Social Acceptance, Athletic Competence, Physical Appearance, and Behavioural Conduct; and one global self-worth scale. The Athletic Competence, Physical Appearance and Global Self-worth subscales will be used in the current study. It has been validated in samples of children from a wide range of cultural backgrounds, including in Australian children and has high levels of internal consistency. Harter [83] reported factor-analytic data that confirmed the use of these subscales and good internal reliabilities which have been replicated in other studies [84].

## *Quality of life*

Quality of life will be assessed with the Paediatric Quality of Life – Teen Report (PedsQL) [85]. The PedsQL is a 23-item self-report quality of life measure for 13-18 year olds. This measure has been demonstrated to have good validity and reliability [86].

## *Additional information*

Socioeconomic status will be characterised by the Index of Relative Socioeconomic Advantage Disadvantage (IRSAD) developed by the Australian Bureau of Statistics (ABS) using 2001 national census data. The IRSAD is a general socio-economic index based on 21 measures of both disadvantage and advantage including annual household income, persons over 15 educational attainment, employment status, unskilled vs. skilled occupations, number of bedrooms in dwelling, percentage of one parent families, value of weekly rent, private dwelling with no car, ownership of residing dwelling, value of weekly mortgage repayments, private dwellings with internet and number renting from government or not for profit agency. Scores with low index values indicate areas of disadvantage and high values indicate areas of advantage. Ethnicity will also be recorded.

**Instruments: Outcome measures for parent**

Parents will complete the several of the same assessments (activity questionnaire, meeting guidelines questionnaire, physical activity enjoyment questionnaire) along with adult versions of questionnaires covering the moods and feelings area (DASS-2121). The DASS-21 is a short-form of the Depression, Anxiety and Stress Scale (DASS) [87]. The DASS has been shown to reliably distinguish between symptoms of depression, anxiety and stress in clinical [88] and non-clinical samples [87]. The DASS-21 has been demonstrated to have acceptable reliability and validity [89].

*Family Outcome Measure*

Parents will also complete the general functioning scale of the McMaster Family Assessment Device (FAD) [90]. The FAD is a 53 item self-report which assesses family functioning on five subscales; problem-solving, affective responsiveness, affective involvement, behaviour control and general functioning. The FAD is suitable to be administered to all members of a family over 12 years, and has adequate internal consistency, test-retest reliability and concurrent validity [90-91].

Families will be interviewed on site and invited to discuss their family lifestyles, including discourses of gender, ethnicity, socioeconomic status and education; attitudes to food, eating and exercise in order to identify challenges and barriers to change. These activities will be conducted in collaboration with the research team to identify and explore means of achieving change for the adolescents and families. Families will be visited at home to observe lifestyle and potential resources in achieving change. These qualitative assessments will augment the results of the quantitative measures, and provide the opportunity to discuss discrepancies.

## Analysis plan

Process evaluation will use descriptive statistics and qualitative analysis.

Impact and outcome evaluation will use a multi-level mixed modelling approach for the hierarchical data collected over the one-year observational period (repeated measurements of individuals nested within families.) Estimates of change in outcomes over time periods will be adjusted for potential confounders of age, gender, maturation level, IRSAD and parental education levels. All change estimates will be presented as adjusted mean change with corresponding 95% confidence intervals. Non-normally distributed data will be appropriately transformed as necessary, and statistical models checked for unduly influential outliers. All data analysis will be performed utilising current statistical software (Stata/IC 10.1 for Windows, Statacorp).

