**Activity behaviours**

On an individual level, an imbalance between energy intake and energy expenditure can lead to obesity [14]. A change in energy balance is required to achieve weight loss outcomes, by either increasing energy expenditure through physical activity or reducing energy intake or ideally a combination of both. Achieving this outcome in adolescents is further complicated by the need to recognise that growth is still occurring. Kemper et al. [15] conducted a longitudinal study measuring body-mass index (BMI) and lifestyle factors from the age of 13 until 27 years. Their results demonstrated a strong relationship between high levels of physical activity and low body mass. Berkey, Rockett, Gillman and Colditz [16] conducted a large one-year prospective study and found that increased physical activity was associated with decreases in BMI in girls and overweight boys. Increases in sedentary behaviour were associated with increases in BMI.

The research above supports the utilisation of physical activity as a key component in adolescent obesity treatment. Interestingly the results from Anderson et al.,[17] suggested that targeting sedentary behaviour may significantly improve outcomes. Results from a study by Epstein et al. [18] support this proposition. In their randomised controlled trial with 8 – 12 year olds, participants were allocated to a treatment group which either targeted physical activity, sedentary behaviour or both. At twelve month follow-up the sedentary behaviour group had significantly greater weight reduction than the other two groups. These results have yet to be replicated with adolescent participants.

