# Participant recruitment procedures: Adolescents and their families will be recruited via the health system, the education system and from the general community. Paediatric specialists and allied health professionals will be asked to identify potentially suitable adolescents. Print and radio mass media will be used to inform the general community of the study. In addition to these sources, participants will be recruited from workplaces that employ a large number of adolescents, within the Perth metropolitan area using the snowball technique [36]. Volunteers will be screened to ensure they meet the inclusion and exclusion criteria. Inclusion criteria will be: males and females aged 12-16 years; body mass index higher than the 85^th^ percentile (includes children who are typically classified as overweight or obese; [37]). Children will be excluded if they: are obese due to identified genetic factors; have morbid obesity (BMI z score higher than 3.5); have a metabolic/endocrine disease; are unable to attend twice weekly sessions, are undergoing treatment for psychiatric disorders or are assessed as unsafe to participate. Volunteers will be approved for participation by their medical practitioner.

**Sample size:** A sample size of 96 is required at post test in the intervention group to detect a 20% difference in the outcome variables at 80% power and 5% level of significance. A small effect size (0.2) is assumed for studies on behavioural effects due to the influence of extraneous variables and the subtleties of human performance. Allowing for an attrition rate of 30%, 124 adolescents and their families will be recruited into the intervention.

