**Evaluation**

There is substantial agreement that interventions for overweight young people need to be evaluated in terms of process and outcome and not just immediate impact (Livingstone et al 2007) to understand not only how much the intervention works but why and for whom.

**Process evaluation:** A broad process evaluation will be conducted in line with the recent framework for mandatory evaluation to ensure well informed public policy decisions [38] and recommendations by the recent Cochrane review for obesity interventions [11]. Questionnaire surveys of participants, focus groups of participants and program facilitators are anticipated [39].

Program fidelity will be assessed through observations of sessions, review of program notes and focus groups with program staff [40]. Program dose will be assessed by attendance records. Barriers to participation will be explored through participant/parent surveys including reasons for non attendance and gaining reasons for drop out from those who do not complete the program [41]. Participant satisfaction will be assessed with a validated tool [42] along with focus groups. Monitoring will also be conducted for potential adverse effects, specifically: changes in linear height, disordered eating, and psychological well being [11].

**Impact evaluation:** Immediate impact of the intervention will be assessed by comparing the changes over the 3 months between pre program assessment and immediately post program assessment with any changes over the 3 months ‘wait-list’ period between initial assessment and pre program assessment.

The primary impact measures will be changes in: 1) leisure time spent in light and moderate/vigorous physical activity; 2) leisure time spent in sedentary activity; 3) number of weekly serves of fruit and vegetables and 4) number of weekly serves of extras.

Secondary impact measures will include: readiness to change state, exercise self efficacy and food self efficacy, meeting of sedentary screen time, vigorous physical activity and key diet target behaviours.

**Outcome evaluation:** The longer term changes in behaviour (same variables as short term impact), as well as physical and mental well being and family functioning, will be assessed by comparing changes between assessments at baseline and at 3, 6 and 12 months post intervention.

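### Change in height is a named harm in growing 12-16 year olds, but the protocol gives it no expected-growth reference and no wait-list comparison, so slowed growth could go unrecognised

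*Protocol*

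**What the plan says.** - **The harm.** The process evaluation paragraph of the Evaluation section says: "Monitoring will also be conducted for potential adverse effects, specifically: changes in linear height, disordered eating, and psychological well being". The Aims also list adverse outcomes among the things that process evaluation will assess.
- **Its analysis.** The Analysis plan opens with "Process evaluation will use descriptive statistics and qualitative analysis".
- **The other track.** Impact and outcome evaluation receive a multi-level mixed model, in which "Estimates of change in outcomes over time periods will be adjusted for potential confounders of age, gender, maturation level, IRSAD and parental education levels". Results are adjusted mean changes with 95% confidence intervals. The comparison of program-period change with wait-list change is written under impact evaluation.
- **Height.** It appears under Adiposity: "Weight, height and waist circumference measurements will be made using calibrated scales, stadiometer and inelastic tape measure and standardized protocols". Standardisation follows for BMI: "Body mass index will be calculated and age and sex adjusted BMI z-scores determined to enable comparison with state-wide surveys". Nothing equivalent is said of height.
- **Population.** Eligible are "males and females aged 12-16 years", and the Background (Activity behaviours) acknowledges "the need to recognise that growth is still occurring".

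**The concern.** A harm measure must be able to separate harm from no harm. In adolescents who are still growing, the change in height is expected to be positive in both cases. What carries the information is the shortfall against expected growth, and that needs either a growth reference or a control interval. The protocol has both tools (standardised scores and a 3-month wait-list period) but directs neither to height.

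The other two named harms are better placed. Psychological well-being has the Moods and Feelings questionnaire and eating style has the Dutch Eating Behaviours Questionnaire. Both are listed as adolescent outcome measures and so can reach the adjusted model. Linear growth is not named as an outcome in its own right. The protocol's Summary presents monitoring of adverse effects as part of its answer to gaps found by a systematic review, and for growth the plan as written does not secure that answer.

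**Working it through.** The protocol states no growth rate, height SD or harm threshold, so there is no figure to reproduce. The arithmetic below is illustrative.

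**Inputs from the protocol.** The wait-list interval is 3 months and the program interval is 3 months (Study design). The last assessment is 12 months post program, so it falls 3 + 12 = 15 months after the second pre-program assessment. The number required at post-test is n = 96 (Sample size).

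**Assumptions.** Normal growth velocity v is 0.5 to 9 cm/year. The harm scenario is a halving of v. The population SD of height is 6 to 8 cm. Measurement SD s is 0.2 to 0.5 cm. The SD w of true within-person variation in the contrast is 0.3 to 0.6 cm.

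**Step 1: what an unreferenced height change would show.** Expected gain = v × t; halved gain = v × t / 2.

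| v (cm/year) | 3 months, expected (cm) | 3 months, halved (cm) | 15 months, expected (cm) | 15 months, halved (cm) |
|---|---|---|---|---|
| 1 | 0.25 | 0.125 | 1.25 | 0.625 |
| 3 | 0.75 | 0.375 | 3.75 | 1.875 |
| 5 | 1.25 | 0.625 | 6.25 | 3.125 |
| 7 | 1.75 | 0.875 | 8.75 | 4.375 |

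Over the whole assumed range of v, the halved gain runs from +0.0625 to +1.125 cm at 3 months and from +0.3125 to +5.625 cm at 15 months. It is always positive.

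**Step 2: what a growth reference would show.** At 5 cm/year the 15-month shortfall is 6.25 − 3.125 = 3.125 cm. As a height z-score this is a fall of 3.125/8 = 0.39 to 3.125/6 = 0.52. The same data that read as a gain in cm read as a clear loss once standardised.

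**Step 3: what the wait-list contrast would show.** With heights H1 and H2 before the program and H3 after it, the contrast is (H3 − H2) − (H2 − H1) = H3 − 2·H2 + H1. Its measurement-error variance is (1 + 4 + 1)s² = 6s². Hence SE = √(6s² + w²)/√96.

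- Smallest assumed SDs (s = 0.2, w = 0.3): √0.33/√96 = 0.059 cm.
- Largest assumed SDs (s = 0.5, w = 0.6): √1.86/√96 = 0.139 cm.

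Halving shifts the contrast by v/8. Power is approximately Φ(v/(8·SE) − 1.96), two-sided 5%:

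| v (cm/year) | Shift (cm) | Power over the assumed SDs |
|---|---|---|
| 1 | 0.125 | 0.14 to 0.57 |
| 3 | 0.375 | 0.77 to >0.99 |
| 5 | 0.625 | at least 0.99 |

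**Step 4: why the contrast in cm is not enough alone.** Growth velocity also falls naturally. If it drops by 2 cm/year per year (assumption), velocity is 2 × 0.25 = 0.5 cm/year lower one quarter later, and the second 3-month gain is 0.5 × 0.25 = 0.125 cm smaller with no harm at all. That equals the whole harm signal at 1 cm/year. Standardising for age and sex removes part of this. Timing of puberty accounts for more, and for that the planned maturation adjustment is needed. For the 15-month change there is no control interval of matching length, so the growth reference is the only comparator.

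**The case against.** A reader might infer three stronger things, and the document supports none of them.

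- **That height is analysed in raw centimetres and that any gain would count as no harm.** The protocol gives no scale for the height change and no decision rule. Its acknowledgement that growth continues makes so naive a reading less likely.
- **That descriptive statistics cannot show slowed growth.** They can. A mean z-score change, a velocity, or mean height change by interval are all descriptive.
- **That the contrast needs no new measurement.** No section says height is taken at every assessment. Physical status is placed under outcome evaluation (baseline and 3, 6 and 12 months post program), not under the wait-list versus program comparison.

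It can also be argued that height is measured under adolescent outcome measures, that outcome evaluation covers physical well-being, and that scale and reference are details for an SAP, which was not available. Part of this stands: nothing forbids a good analysis of height. But the protocol is not simply silent. It contains its own analysis plan, places adverse outcomes in one track, and gives the comparison, adjustment and intervals to the other. An SAP that follows it has no instruction to bring height across.

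Finally, every growth rate and SD used here is assumed, and a halving is a scenario rather than an expectation for an 8-week program that focuses on healthy behaviours rather than weight management. That limits the size of the point, not its direction.

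**Conclusion.** The point holds in a limited form. As assigned, the growth harm has no expected-growth reference, no wait-list comparison and no adjusted estimate, so slowed growth could go unrecognised. Whether it would depends on choices the protocol leaves open. The direction, that halved growth still shows as a gain, follows for any positive growth rate. The size is only illustrative, since the documents supply none of the growth figures. No primary impact measure is affected; what is at stake is the study's ability to report on one of its three named harms in minors. A correction should be made, and it is a modest one.

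**What to change.** 1. In the process evaluation paragraph, define the growth measure as change in age- and sex-standardised height (z-score), as is already done for BMI, and name the reference.
2. In the Analysis plan, state that this measure enters the mixed model already planned, with the planned maturation adjustment and 95% confidence intervals. Report two estimates: program-interval change minus wait-list-interval change, and change from pre-program to 12 months post program.
3. Confirm that height is measured at both pre-program assessments and immediately post program. Without all three the first estimate cannot be formed.
4. Keep descriptive and qualitative methods for fidelity, dose and satisfaction.

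The cost is protocol wording and one more derived variable. If step 3 shows that height was not scheduled at one of those visits, a stadiometer reading is added there. The limit to state openly is precision: in participants near the end of growth the wait-list contrast will be weak, so an interval that includes no change should not be read as evidence of no slowing in them.
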